**Methods:**

A randomized controlled three-group pre- and posttests experimental design is proposed. This study plans to recruit 204 first-time mothers on their day of discharge from a public tertiary hospital in Singapore. Eligible first-time mothers will be randomly allocated to either a Web-based psychoeducation group, a home-based psychoeducation group, or a control group receiving standard care. The outcomes include maternal parental self-efficacy, social support, psychological well-being (anxiety and postnatal depression), and cost evaluation. Data will be collected at baseline, 1 month, 3 months, and 6 months post-delivery.

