### Hypotheses

The hypotheses are as follows:

When compared with mothers in the control group, mothers in Web-based and home-based psychoeducational intervention groups will report a significantly:higher level of self-efficacy,higher level of social support received,lower level of anxiety and depression, andhigher level of satisfaction with postnatal services.When compared with those in the home-based psychoeducational intervention group, mothers in the Web-based psychoeducational intervention group will not report significantly poorer aforementioned maternal outcomes.It is more cost-effective to provide a Web-based psychoeducational intervention than a home-based psychoeducational intervention and routine care.

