### Sample Size Determination

In similar studies, psychosocial and educational interventions have resulted in a medium effect size on outcomes similar to this study [44,52,62]; hence, the study intervention was regarded to have a medium size effect on outcome variables. On the basis of a power analysis, to achieve a medium effect size of 0.55, using a power of 80% and a significance level of 5% (2-sided), 52 participants would be needed in each group [63]. Although a dropout rate of 30% was reported by a previous study [52] and our preliminary study [46], we anticipated a lower dropout rate of 24% in this study because of better communication channels established with participants (eg, using social media such as WhatsApp to remind participants, follow-up questionnaire conducted through a Web-based survey). Therefore, a minimum sample of 204 (52×3/0.76) participants with 68 in each group was needed. For process evaluation, a purposive sampling of 45 participants (15 from each group) with different posttest 1 self-efficacy scores (5 high, 5 moderate, and 5 low scores from each group) were invited to participate in a process evaluation interviews, or until data saturation was achieved.

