### Study Procedure

Data collection commenced after the ethical approval had been obtained. The nurse in charge was contacted to determine the physical and psychological well-being of potential participants. After confirming the inclusion criteria, the participants were approached at the postnatal inpatient wards. Only after obtaining written consent would the mother be recruited into the study. This was followed by a collection of demographic data and baseline data via a self-administered questionnaire before randomization takes place. Outcomes were measured at the following time points for all participants in all three groups: (1) after delivery and before discharge (baseline data), (2) immediately after the intervention (posttest one, at the end of 1 month post delivery), (3) 2 months after the intervention (posttest 2, 3 months post delivery), and (4) 5 months after the intervention (posttest 3, 6 months post delivery).

RA1 made a visit to the hospital regularly to recruit participants and was responsible for informing all participants of their allocated group, and collection of baseline data for all participants. RA1 provided participants in the Web-based intervention group with Web access (individual username and password) for 1 month. For participants assigned to the home-based intervention group, RA1 provided the educational booklet before discharge and arranging home visits at about 5 to 10 days post delivery, as this is the most crucial period for mothers, as well as 3 telephone calls [71].

RA2 was responsible for the Web-based postnatal psychoeducational intervention (eg, providing expert advice in group discussion forums and confidential corner, and 3 reminder phone calls). RA2 was responsible for the collection of all posttest data, including process evaluation interviews.

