To answer the hypothesis 1, repeated measures ANCOVA, adjusted for confounding variables (eg, age, ethnicity), will be used to test the effects of both interventions on maternal self-efficacy, social support, postnatal depression, and anxiety across four time points. Univariate ANCOVA will be used to test the difference of each of the three outcomes among three groups at each posttest time point by adjusting for confounding factors (eg, baseline data, age, and ethnicity). Chi-square test or Poisson regression will be used to determine maternal satisfaction with the postnatal supportive care at each posttest time points. To answer hypothesis 2, a 95% CI of the mean difference of maternal self-efficacy scores will be calculated. If the lower boundary is more than −5, the hypothesis will be accepted. To address hypothesis 3, we will calculate the base case incremental cost-effectiveness ratios (ICER) of the two intervention groups compared with the control group. We captured the 6-month costs at three posttest time points: (1) health care system perspectives, including service providers that mothers consumed because of maternal and/or neonatal related conditions such as GP clinic, polyclinic, private clinic, hospital out-patient, hospital Accident and Emergency and (2) participant’s out-of-pocket cost of transportation fee for these visits. In addition, fixed costs (also considered health care system perspectives) such as development and implementation of Web-based intervention, delivery of home-based intervention, and training of RAs were also captured. The effectiveness of the intervention on four outcomes (namely self-efficacy, social support, depression and anxiety) will be calculated. The ICERs for each outcome will be plotted in the cost-effectiveness plane to examine the dominance and extended dominance, and then the cost-effectiveness acceptability curves will be generated to demonstrate the cost-effectiveness of the alternatives using difference willingness-to-pay thresholds [72-78].

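### As worded, the Web-versus-home decision on self-efficacy uses a mean difference with no baseline term, although baseline scores are available and the hypothesis 1 posttest ANCOVAs adjust for them

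*Protocol article*

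**What the plan says.** Hypothesis 2 (Hypotheses section) is that, compared with the home-based group, "mothers in the Web-based psychoeducational intervention group will not report significantly poorer aforementioned maternal outcomes". The Data Analysis section turns this into a rule on one outcome: "To answer hypothesis 2, a 95% CI of the mean difference of maternal self-efficacy scores will be calculated". The rule continues: "If the lower boundary is more than −5, the hypothesis will be accepted". It names no model, no covariate and no posttest.

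In the same section, for hypothesis 1, univariate ANCOVAs compare the three groups at each posttest "by adjusting for confounding factors (eg, baseline data, age, and ethnicity". The Abstract describes the study as a pre- and posttest design. Study Procedure confirms that a baseline score exists for every mother, since consent is followed by "collection of demographic data and baseline data via a self-administered questionnaire before randomization takes place". Sample Size Determination rests on 52 evaluable mothers per group, "to achieve a medium effect size of 0.55", with 80% power and a two-sided 5% level. It gives no SD for the self-efficacy score (PMPSE), no baseline-to-posttest correlation and no separate calculation for hypothesis 2.

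**The concern.** The section specifies baseline adjustment where it compares groups at each posttest. It then gives hypothesis 2 a self-contained rule, with an estimator and a cutoff, that has no baseline term and does not refer back to the ANCOVA. Followed literally, the rule compares the scores of two independent groups and sets aside what each mother's own starting score predicts.

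Two things are at stake. First, the interval is wider than it need be, so a Web program truly equal to home visits is more likely to miss the −5 cutoff. Second, with about 52 completers per arm, a chance difference in starting self-efficacy carries through to the posttest difference and can move the verdict either way. The Discussion says that a Web program found as effective as home visits and more cost-effective would be proposed as standard care, so the verdict matters.

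**Working it through.** **The plan's own figure.** For two groups, n = 2 × (1.96 + 0.84)² / 0.55² ≈ 52 per group (52.9 with the t distribution). This reproduces the stated 52. For dropout, 52 × 3 / 0.76 = 205.3 against the stated 204, which is close enough not to matter here.

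**Inputs for hypothesis 2.**
- From the article: margin −5; a 95% interval, whose lower limit is a one-sided 2.5% test; 52 completers per arm.
- Assumed: true Web-minus-home difference 0; SD = 5 / 0.55 = 9.09, which treats the margin as equal to the planned effect size (the article does not say this); baseline-to-posttest correlation r from 0.2 to 0.7.

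**Formulas.** Unadjusted SE = SD × √(2/n) = 9.09 × √(2/52) = 1.78. Adjusting for baseline multiplies the SE by √(1 − r²). Power to clear −5 is approximately Φ(5/SE − 1.96). For r = 0.5: SE = 1.78 × 0.866 = 1.54, and Φ(3.24 − 1.96) = Φ(1.28) = 0.90. Age and ethnicity are left out of these figures.

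| Analysis (n = 52, SD 9.09) | SE | Power, normal | Power, t |
|---|---|---|---|
| Unadjusted | 1.78 | 80.1% | 79.3% |
| Adjusted, r = 0.2 | 1.75 | 81.7% | – |
| Adjusted, r = 0.3 | 1.70 | 83.7% | 82.9% |
| Adjusted, r = 0.5 | 1.54 | 89.9% | 89.4% |
| Adjusted, r = 0.7 | 1.27 | 97.5% | 97.3% |

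**Sensitivity to the assumptions (normal approximation).**
- All 68 per arm analysed, SD 9.09, r = 0.5: 89.4% to 95.9%, a gain of 6.6 points before rounding.
- n = 52, r = 0.5, other SDs: 98.9% to 99.8% at SD 6; 89.0% to 95.7% at SD 8; 72.2% to 83.7% at SD 10; 56.5% to 68.9% at SD 12; 44.5% to 55.7% at SD 14.
- Over r = 0.2–0.7 and SD 6–14 at n = 52, the gain runs from 0.2 to about 28 points.

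**Chance baseline imbalance (SD 9.09, n = 52, r = 0.5).** The SE of the baseline difference between arms is 1.78 points. An imbalance of one SE shifts the unadjusted posttest difference by 0.5 × 1.78 = 0.89 points, or 0.89/5 = 18% of the margin. An imbalance of two SEs shifts it by about 1.8 points. In simulation under these assumptions:
- With truly equal arms, the two analyses give opposite verdicts in about 13% of trials (7% at r = 0.3, 19% at r = 0.7).
- In the roughly 15% of trials where Web starts more than 0.2 SD below home, the unadjusted rule passes an equal Web program 52–54% of the time, against 89% adjusted.
- In the roughly 15% where Web starts more than 0.2 SD above home, the unadjusted rule passes a program truly 5 points worse about 8–9% of the time, against about 2% adjusted.
- Over all trials, false acceptance at −5 is about 2.5% with either analysis.

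**The case against.** The strongest reply is that the article never says the difference is unadjusted. An ANCOVA contrast is also a mean difference with a 95% interval, the adjusted model appears a few sentences earlier, and a condensed article may leave such detail to an analysis plan that is not shown. This stands in part: the absence of adjustment is inferred from the wording. But the article does fix an estimator and a cutoff for hypothesis 2, and it names covariates for hypothesis 1 and not here. Two analysts could therefore compute different intervals and reach different verdicts.

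Three stronger readings are tempting, and the documents do not support them.

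- **That the rule is invalid.** Randomization keeps the unadjusted interval at its nominal error rate. The imbalance figures above describe selected tails of chance, and a wider interval makes acceptance harder overall. At the assumed SD, unadjusted power is also about the 80% the trial planned for.
- **That the trial loses a fixed 10 points of power.** That figure belongs to one combination: SD about 9.1, correlation about 0.5 and 52 per arm. The article presents 0.55 as a generic medium effect and does not link it to the 5-point margin. A low correlation is also plausible, because baseline is taken before discharge and the Introduction says the reality of newborn care sets in only afterwards.
- **That the report would carry two conflicting Web-versus-home estimates.** Hypothesis 1 compares each program with control, and its ANCOVA tests differences among three groups. No Web-versus-home contrast is stated there.

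**Conclusion.** The point holds as a matter of efficiency and clarity, not validity. As worded, hypothesis 2 is decided without the baseline score, although that score is collected before randomization and the neighbouring analysis uses it. Adjustment would narrow the interval and reduce the influence of chance baseline imbalance on the −5 verdict, with the overall error rate unchanged.

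The size cannot be fixed from the article. At SD 9.1 and 52 per arm the gain is under 2 points if the correlation is 0.2, about 4 at 0.3, about 10 at 0.5 and about 18 at 0.7. It is smaller if more mothers are retained or the SD is lower. The change is worth making because it is free; the trial does not fail without it.

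**What to change.** Replace the hypothesis 2 sentence with wording such as: *Hypothesis 2 will be assessed with the 95% CI of the baseline-adjusted Web-minus-home mean difference in PMPSE, from the univariate posttest ANCOVA with baseline PMPSE, age and ethnicity as covariates, at [one posttest named by the sponsor]; it is accepted if the lower limit is above −5.* Report the unadjusted interval as a sensitivity analysis.

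The posttest has to be named because an ANCOVA is planned at each of three, and without it up to three intervals could decide the question. Follow-up ended in August 2017, so the wording and the deciding posttest should be fixed before outcomes are compared by arm.

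The cost is one sentence and one extra contrast from a model already planned. No further participants or data are needed. The Results section projects data entry and analysis to finish around March to June 2018, so the change was still open when the article was written.

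### Hypothesis 2 says Web-based is no worse than home-based on every maternal outcome, but it is accepted on self-efficacy alone, against a −5 margin with no stated reason

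*Protocol article*

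**What the plan says.** The Hypotheses section first lists four outcomes on which the two programs should beat control: self-efficacy, social support, anxiety and depression, and satisfaction with postnatal services. Hypothesis 2 then refers back to that whole list: "mothers in the Web-based psychoeducational intervention group will not report significantly poorer aforementioned maternal outcomes".

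The Data Analysis section gives the test: "To answer hypothesis 2, a 95% CI of the mean difference of maternal self-efficacy scores will be calculated". The decision rule follows: "If the lower boundary is more than −5, the hypothesis will be accepted". No rule or margin is given for social support, the EPDS, the HADS-A or satisfaction. No reason is given for 5 points, and none of the three posttests is named as the one that decides.

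The Sample Size Determination section works from a standardized effect of 0.55, "using a power of 80% and a significance level of 5% (2-sided), 52 participants would be needed in each group". It does not mention the margin, give an SD for the PMPSE, or express the effect in PMPSE points.

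**The concern.** The hypothesis and its acceptance rule do not match. A claim about several outcomes is accepted on one. For the others, the only criterion left is the wording of the hypothesis itself, the absence of a significantly poorer result. With about 52 analysed mothers per group, a real disadvantage on depression or anxiety could easily be non-significant.

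The margin raises a second question. A non-inferiority margin should be small relative to the benefit that the reference treatment is expected to deliver. Here the reference is the home program, whose planned benefit is 0.55 SD, yet nothing connects 5 points to 0.55 SD.

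The result matters because the Discussion (Principal Findings) says a Web program found as effective as the home program, and more cost-effective, would be put forward as standard care without home visits. Hypothesis 2 is the formal test behind the words about equal effectiveness.

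**Working it through.** **Scope.** This needs no arithmetic. Hypothesis 2 covers four outcome domains, and the rule uses one. Any Web-minus-home difference on the other three leaves the stated verdict unchanged.

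**Inputs.** Effect 0.55 SD, 80% power, two-sided 5%, 52 per group after the assumed 24% dropout, and 68 per group recruited (Sample Size Determination; Results). Margin 5 points, lower limit of a 95% CI (Data Analysis). The SD of the PMPSE is not in the document, so it is an assumption, shown here from 5 to 12. The difference is read as Web minus home, with higher scores better.

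**The plan's own figure.** n = 2(1.96 + 0.8416)² / 0.55² = 51.9, so 52 per group. This reproduces.

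**Margin against planned effect.** The two are equal when 0.55 × SD = 5, that is SD = 5/0.55 = 9.09.

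**Chance of acceptance.** For a true Web-minus-home difference of −d, P(accept) = Φ[(5 − d)/(SD√(2/n)) − 1.96]. Take d = 0 if Web equals home, and d = 0.55 SD if Web equals routine care while home has its full planned effect. Each pair is for 52 / 68 analysed per group.

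| SD | Planned effect (points) | Margin as % of effect | P(accept), Web = home | P(accept), Web = routine care, home at full effect |
|---|---|---|---|---|
| 5 | 2.75 | 182% | >99% / >99% | 63% / 75% |
| 7 | 3.85 | 130% | 95% / 99% | 13% / 16% |
| 8 | 4.40 | 114% | 89% / 95% | 6% / 6% |
| 9.09 | 5.00 | 100% | 80% / 89% | 2.5% / 2.5% |
| 10 | 5.50 | 91% | 72% / 83% | 1.3% / 1.2% |
| 12 | 6.60 | 76% | 57% / 68% | 0.4% / 0.3% |

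**If home does less than planned.** The rule does not check that home beats control. With 52 per group and Web equal to routine care:

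- Home effect 0.30 SD (illustrative): at SD 9.09, Φ[(5 − 2.73)/1.783 − 1.96] = 25%; at SD 7, Φ[(5 − 2.10)/1.373 − 1.96] = 56%.
- Home effect zero: 80% at SD 9.09 and 57% at SD 12, as in the column for Web = home. Acceptance is then literally true, but it says nothing about whether either program works.

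**If Web keeps half of the planned home benefit** (d = 0.275 SD, 52 per group): it passes 61% of the time at SD 7 and 29% at SD 9.09.

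**A tighter margin.** A margin of half the planned effect would need 2(2.8016)²/0.275² = 207.6, so 208 analysed per group, whatever the SD. The trial cannot support that, so the remedy lies in the wording and interpretation of the claim.

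**The case against.** The strongest reply has four parts.

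- **Other analyses.** Hypothesis 1 tests Web against control separately, so a Web program no better than routine care would be expected to fail there. Depression, anxiety and social support also enter the covariance analyses and the cost-effectiveness ratios, and the Discussion makes adoption depend on cost-effectiveness as well. This stands as a limit on the harm. It does not repair the rule: nothing in the Data Analysis section makes acceptance of hypothesis 2 depend on those results, and a non-significant three-group comparison is not evidence of non-inferiority.
- **The SD is unknown.** A reader might infer that the margin is as large as the whole planned effect. The document does not support that, because it gives the effect only in SD units. The statement is true at an SD of about 9.1 or less and false above it. Nor is it true that the margin concedes the whole effect whenever the rule has adequate power: with 68 per group at SD 10, power is 83% and the margin is 91% of the effect.
- **Passing is not easy if home works as planned.** A reader might infer that a useless Web program would readily pass. If home has its full effect, it passes 2.5% of the time at SD 9.09, and the risk becomes material only at clearly smaller SDs.
- **Condensed article.** Further margins, the deciding time point and the model that supplies the interval may be in the full protocol. That is fair for those details. In particular, the text says only that a mean difference is used, which does not show that it is unadjusted. But the mismatch between hypothesis and rule is stated in the article itself and is not an omission.

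**Conclusion.** The concern holds in three parts of unequal weight.

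The main one rests on the text alone: a no-worse claim over four outcome domains is accepted on self-efficacy, so the verdict is blind to the other three.

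The second is that the margin has no stated reason and no link to the design effect. Its size relative to that effect depends on an SD that the document does not give: 130% at SD 7, 100% at 9.09, 91% at 10 and 76% at 12.

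The third is that acceptance is not tied to either program beating control. This matters most if home visits have little effect, when a Web program equal to routine care could pass often (25% at SD 9.09 with a home effect of 0.30 SD; 80% with none).

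These probabilities assume normal scores, a common SD, 52 analysed per group and no gain from baseline adjustment.

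**What to change.** 1. Restrict hypothesis 2 and its acceptance to PMPSE at one named time point. For social support, EPDS, HADS-A and satisfaction, report Web-minus-home confidence intervals without a non-inferiority claim, or give each its own margin. For EPDS and HADS-A, where higher is worse, the upper limit decides.
2. State the reason for −5 in PMPSE points, against an SD and an expected home-versus-control effect drawn from sources other than this trial's outcome data.
3. Interpret acceptance together with the Web-versus-control PMPSE result from hypothesis 1, and report what share of the home-minus-control effect the lower limit preserves.
4. State that the interval comes from the baseline-adjusted ANCOVA already planned.

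The cost is a few sentences before the analysis, with no new data. The price is a narrower claim that is harder to make: the trial could support a statement about self-efficacy, but not one about maternal outcomes in general.

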### Ethical Considerations

Ethics approval for the study was received from the relevant ethics review board before commencing the study (Ref: 2015/01189) on 25 January 2016. A participant information sheet, which provides a brief introduction to the study as well as the benefits and risks of their participation in the study was explained. Anonymity and voluntary participation was ensured. Each participant’s written consent was also obtained, including consent for audio recording during the process evaluation interview. Participants whose EPDS scores were more than 13 were referred to their obstetrician for further follow-up. A token of appreciation was provided to all participants for their time spent to participate in the study and this is a common practice in the study country.

## Results

The booklet for the home-based intervention group and the website for the Web-based intervention (including the audio and video files) have been developed. The recruitment of participants started in October 2016 and was completed in February 2017 with 68 mothers in each group (n=204). All follow-up data were collected by August 2017. The consolidated standards of reporting trial flowchart can be found in Figure 1. The projected timeline for completion of data entry and data analysis is around March to June 2018.

